### 2.9. Program Evaluation

An implementation/program evaluation of this new transdisciplinary allied health service model (EAHOP intervention) to address poor outcomes associated with falls and frailty for people entering and living in residential aged care will also be conducted. See Table 4 for details. The evaluation objectives are as follows:To ascertain if the transdisciplinary model has met the project aim of improving quality of care.To identify barriers and enablers to implementation of the program as planned, with the aim of developing an implementation guideline.To provide a detailed description of program resourcing.

**Table 4 healthcare-13-00341-t004:** Summary of the evaluation process.

Implementation Outcome	Measurement Details
Feasibility	Descriptive: size of RAC home and staffing Description of all interventions delivered Cost per client (of total allied health service and per allied health service) Qualitative data from key stakeholder interviews
Access and Uptake	Number of referrals Number of consented participants Occasions of service (how many times seen) per allied health discipline (AH) and allied health assistant (AHA) per resident and discipline Units of service, direct and indirect time in minutes per resident and discipline Time spent on case conferences
Acceptability	Interviews re: experiences of stakeholders Service managers Care home staff ×10 Allied health professionals (all) Allied health assistants (all) Carers ×15 Participants ×15 GP/s

### 2.10. Economic Evaluation

An economic evaluation of the EAHOP intervention will be measured by calculating the Quality-Adjusted Life Year (QALY) using data from the QOL-ACC. The costs of staff (including on-costs and overhead costs) involved in the intervention will be enumerated, and cost savings due to expected reductions in hospitalisations and falls will be estimated by comparing the RAC hospital leave days for those involved in the intervention as compared to an age-, sex-, and level-matched sample.

### 2.11. Fidelity Assessment

Fidelity to the intervention will be assessed using Hasson’s Conceptual Framework [33]. The percentage of consented participants triaged through case conferencing will be reported. At the discipline level, at least 10% of all participants will be randomly sampled and evaluated for accuracy against content, frequency, and duration of intervention. Fidelity rating at the intervention level and discipline level will be reported as high/medium/low.

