#### 2.4.2. Case Conferencing

The allied health professionals will conduct their discipline-specific, secondary outcome measures during the baseline period and then make recommendations to be discussed at a case conference. The case conference will be attended by the resident’s General Practitioner, the research clinical liaison manager, and where possible the resident and family member. A plan of action will be agreed with the resident and their family following the case conference that could involve one or more allied health interventions depending on the needs of the resident.

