### 2.6. SampleSsize

The sample size was calculated using R based on 1000 simulated versions of the study, where the power estimate is the proportion of simulated studies that gave *p* < α for the difference between the pre- and post-intervention stages. Using the Short Physical Performance Battery (SPPB) as the primary outcome measure with 50 subjects, the increased mean responses anticipated with alpha 0.01 are shown in Table 2. This is assuming the following parameters: average response at baseline 5; between-subject SD 2.5; variability in effect between subjects SD 2 (so the effect is 2.5 with SD of 2); within-subject SD of 1; and between-group SD of 2 [18].

We expect up to 60 existing residents will consent to the intervention. The site estimates that 20 new residents will enter the home during the study period, and we estimate 15 of these new residents will consent to the study. With a 20% dropout and loss to follow-up, the highest number of participants to complete the intervention is 60 participants.

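### Discipline-level fidelity may rest on as few as 10% of participants (about 6 of 60), although sessions and minutes are already logged for every resident and discipline

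*Protocol article*

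**What the plan says.** Protocol article, section 2.11 (Fidelity Assessment), sets the discipline-level check: "at least 10% of all participants will be randomly sampled and evaluated for accuracy against content, frequency, and duration of intervention". The result is a three-level label: "Fidelity rating at the intervention level and discipline level will be reported as high/medium/low". The article gives no cut-points for the labels.

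Section 2.9, Table 4 (Access and Uptake), lists occasions of service for each discipline and resident, and also "Units of service, direct and indirect time in minutes per resident and discipline". No sampling is mentioned for either.

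Section 2.4.2 says that a resident's agreed plan "could involve one or more allied health interventions depending on the needs of the resident". Not every participant therefore need receive every discipline. In Table 1 the dietetics intervention is limited to participants with weight loss or at risk of malnutrition.

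The base for the 10% comes from section 2.6: "We expect up to 60 existing residents will consent to the intervention"; of the new residents, "we estimate 15 of these new residents will consent to the study"; and after attrition "the highest number of participants to complete the intervention is 60 participants".

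**The concern.** Fidelity is to be judged on three dimensions: content, frequency and duration. Table 4 records the delivered side of frequency and duration for everyone. Rating those two on a small random sample adds sampling error that the study's own records make unnecessary. Only content needs a manual review, and so a sample.

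There is also a question of sampling frame. A rating for a discipline has to come from residents who received it, but the stated base is all participants. If one sample is drawn from that base, a discipline given to only some residents may be represented by very few people.

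At stake is how far the discipline-level labels can be trusted. In a single-home pre-post study, readers will use them to judge whether each part of the model was delivered as planned. Section 2.9 also names barriers and enablers to delivery as planned among its evaluation objectives.

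**Working it through.** **Inputs.** Section 2.6: up to 60 existing and 15 new consenters, and "With a 20% dropout and loss to follow-up". Section 2.11: a sampling floor of 10%. Section 2.1: six groups of up to 10, so up to 60.

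**The plan's own figure.** (60 + 15) × (1 − 0.20) = 60, which reproduces the stated maximum of completers.

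**Size of the fidelity sample at the floor.** 0.10 × 60 = 6. If all 75 consenters are the base, 0.10 × 75 = 7.5, so 8.

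**Precision at the floor.** Assumption: each sampled resident is scored adherent or not. Exact (Clopper-Pearson) 95% limits solve P(X ≥ x | p) = 0.025 for the lower bound and P(X ≤ x | p) = 0.025 for the upper. For 5 of 6:
- lower: 6p⁵(1 − p) + p⁶ = 0.025, so p = 0.359
- upper: 1 − p⁶ = 0.025, so p = 0.975^(1/6) = 0.996

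| Result | Exact 95% interval | Allowing for a finite 60 (or 75) |
|---|---|---|
| 3 of 6 | 12–88% | 13–87% |
| 4 of 6 | 22–96% | 25–93% |
| 5 of 6 | 36–99.6% | 38–98% |
| 6 of 6 | 54–100% | 57–100% |
| 7 of 8 | 47–99.7% | 49–99% |

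**What this does to the labels.** The article gives no cut-points, so I assume high is at least 80% and low is below 50% of sampled residents. With 6 drawn from 60, of whom M are adherent, the number adherent in the sample is hypergeometric. High requires 5 or 6 of 6; low means 2 or fewer.
- True 70% (M = 42): P(high) = [C(42,5)·C(18,1) + C(42,6)] / C(60,6) = (15,312,024 + 5,245,786) / 50,063,860 = 0.41. A medium discipline is labelled high 41% of the time.
- True 80% (M = 48): P(high) = 0.66, so it is labelled below high 34% of the time.
- True 40% (M = 24): P(low) = 0.54, so it is labelled medium or high 46% of the time, but high only about 3%.
- True 90% (M = 54): P(low) is below 1%.

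With 8 of 75 the pattern is similar: true 80% is labelled below high about 50% of the time (7 of 8 are then needed for high), and true 40% is labelled medium or high about 40%.

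**Recipients in one sample of 6 from 60.** Uptake by discipline is not in the article, so this is a range under assumption:

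| Assumed share receiving the discipline | Expected recipients among 6 | P(2 or fewer) | P(none) |
|---|---|---|---|
| 75% (45 of 60) | 4.5 | 3% | <0.1% |
| 50% (30 of 60) | 3.0 | 34% | 1% |
| 25% (15 of 60) | 1.5 | 84% | 16% |

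**With the logs.** Rating frequency and duration on all participants leaves no sampling error in the share treated as planned. Enlarging the sample instead helps slowly. The finite-population interval is 55–97% for 10 of 12 and 72–92% for 25 of 30, against 38–98% for 5 of 6.

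**The case against.** Several points on the other side are sound.

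- **10% is a floor.** The team may sample more. That stands, and the figures above describe the minimum. The article commits to no more than that.
- **High and low are not confused.** A reader might infer from the wide intervals that the labels cannot tell high from low fidelity. The calculation does not support this: outright swaps occur about 3% of the time or less under the assumed bands. The errors lie between neighbouring bands.
- **The frame is ambiguous.** The sentence is introduced as applying at discipline level, which may already mean a separate sample for each discipline. Table 1 describes most disciplines for participants generally and restricts only dietetics. A reader might infer that some disciplines will have one sampled recipient or none. The article gives no uptake figures to support that.
- **Delivery is recorded for everyone anyway.** A reader might infer that the study could not tell an ineffective model from an undelivered one, or that its guidelines hang on these labels. Neither follows. Table 4 supplies full delivery data whatever the audit size, and section 2.9 links the implementation guideline to barriers and enablers.
- **Logs show what was delivered, not what was prescribed.** Plans are individually tailored, so prescribed amounts may have to be extracted. This stands as a cost. It is limited, because Table 1 already fixes several planned amounts: SUNBEAM at 2 h per week for 25 weeks, weekly virtual cycling for those not suited to it, and pharmacist follow-up at 2 weeks and then every 3 months.
- **A graded score over many sessions would carry more information** than adherent or not. True, but the resident remains the sampling unit.
- **An article may leave cut-points and stratification to the full protocol.** Accepted; their absence is not part of this point. The point is the choice the article does state: all three dimensions are rated on a sample.

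**Conclusion.** The point holds as a modest improvement to the process evaluation. Section 2.11 allows discipline-level frequency and duration to be rated on about 6 of 60 residents (8 of 75) when Table 4 already logs sessions and minutes for all of them. At that minimum, 5 of 6 is compatible with anything from about 36% to 99.6%, and under the assumed bands adjacent labels are confused roughly a third to nearly half of the time for true values of 40%, 70% and 80%. This rests on the minimum sample being used, on all-or-none scoring per resident, and on my cut-points. The few-recipients problem is conditional: it needs the single-sample reading and partial uptake, and ranges from negligible at 75% uptake to serious at 25%. The primary analysis is untouched.

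**What to change.** In section 2.11:

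1. Rate frequency and duration for all participants, by discipline, from the service logs listed in Table 4. Compare delivered sessions and minutes with the planned amounts in Table 1 where these are fixed, and otherwise with the resident's agreed plan.
2. Keep the random-sample review for content only. Draw it among the recipients of each discipline, with a stated minimum number per discipline chosen for the precision wanted.

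The cost is some extra analysis of data the study records anyway and, for individually tailored plans, extraction of the prescribed amounts resident by resident. The content review can stay about its present size, but its labels then remain imprecise and should be reported with the number of residents reviewed.

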## 3. Data Analysis

### 3.1. Quantitative Analysis

All statistical analysis will be conducted using R version 4.2.1 (23 June 2022) in Rstudio (version 2023.6.2.561). Baseline demographic and descriptive statistics will be summarised for each group prior to the intervention starting (control phase). Primary outcome measures will be collected twice in the control period at week 0 and week 6. Primary outcome measures will be collected every 12 weeks during the intervention (weeks 12, 24, and 36) and at 12 weeks and 24 weeks post-intervention for each group. Categorical data will be summarised using frequency statistics and will be visualised. Continuous and other numerical data will be visually explored and summarised using sample descriptive statistics, selected as appropriate based on apparent distributions. A mixed-effects model will be computed, with treatment stage (i.e., pre- vs. post-intervention) as a fixed effect and subject as a random effect. Sensitivity analyses will be conducted, which will impute missing data using the “mice” package (version 3.15.0) [34].

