## 2. Methods

### 2.1. Study Design

This is a pragmatic, non-randomised, pre–post design study where six groups of up to 10 participants will start the intervention at different times. Each group will commence a baseline period lasting six weeks. Primary outcome measures will be administered in week 0 (−t_1_) of the baseline period and in week 6 (−t_2_) of the baseline period. The allied health professionals will conduct assessments using the secondary outcome measures during the baseline period, making recommendations for consideration at the case conference held with the resident’s usual General Practitioner. The prescribed allied health intervention/s will last a maximum of 36 weeks with primary outcome measures taken during the intervention period at 12 (t_1_), 24 (t_2_), and 36 (t_3_) weeks, then at 12 (t_4_) and 24 (t_5_) weeks post-intervention. The case conferences will take place in week 1 or week 2 of the intervention period. The timing of the secondary outcome measures will vary depending on the mix of interventions chosen by the allied health professional and the participant needs. See the Supplementary file for further details.

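### The SPPB power simulation includes a between-group SD of 2, but the planned mixed model has no group term, so the model that was sized is not the model to be fitted

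*Protocol article*

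**What the plan says.** Section 2.1 sets out a single-arm pre-post design in which "six groups of up to 10 participants will start the intervention at different times". These staggered start groups are the only groups that the design defines.

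Section 2.6 sizes the study by simulation: "Using the Short Physical Performance Battery (SPPB) as the primary outcome measure with 50 subjects", alpha 0.01. Besides the baseline mean of 5, its inputs are "between-subject SD 2.5", an SD of 2 for variation in the effect between residents, and "within-subject SD of 1; and between-group SD of 2". Table 2 reports power of 0.99, 0.94, 0.84 and 0.63 for mean increases of 2.5, 2, 1.75 and 1.

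Section 3.1 gives the analysis: "A mixed-effects model will be computed, with treatment stage (i.e., pre- vs. post-intervention) as a fixed effect and subject as a random effect". It names no group, group-by-stage or calendar-time term.

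**The concern.** Group counts as a source of variance when the study is sized and is absent when it is analysed. Whether that matters depends on where the SD of 2 acts.

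- **On SPPB level.** Each resident stays in one group, so the group's level drops out of that resident's pre-post difference. Leaving group out is then harmless, but the SD of 2 cannot influence power and should leave no trace in Table 2.
- **On the pre-post change.** Residents of one group then share part of their change. The stated model treats about 50 changes as independent although the shared part comes from six groups. The standard error is too small and the test too liberal.

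At stake are the validity of the SPPB p-value and interval, and whether the powers in Table 2 can be attained by a valid test.

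**Working it through.** **Inputs.** From section 2.6: 50 residents, resident SD of effect 2, within-resident SD 1, group SD 2, alpha 0.01. From sections 2.1 and 3.1: six groups, 2 baseline visits, 3 visits during the intervention and 2 after it. Assumptions: two-sided alpha (sidedness is not stated); post means either the 3 intervention visits or all 5 later visits; group sizes 9, 9, 8, 8, 8, 8; the subject random effect is an intercept only, unless stated otherwise.

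**1. Table 2 with the SD of 2 on level.** The variance of one resident's mean change is 2² + 1² × (1/2 + 1/3) = 4.83, so SE = √(4.83/50) = 0.311. Power of a resident-level test is Φ(increase/SE − 2.576):

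- increase 2.5: above 0.999
- increase 2: Φ(6.43 − 2.576), above 0.999
- increase 1.75: Φ(5.63 − 2.576) = 0.999
- increase 1: Φ(3.22 − 2.576) = 0.74

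With only one visit before and one after, SE = √(6/50) = 0.346, and the powers are 1.00, 1.00, 0.99 and 0.62. Neither version gives 0.94 and 0.84. An intercept-only model rejects more often still.

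Working back from Table 2, SE = increase/(z(power) + 2.576), which gives 0.51, 0.48, 0.49 and 0.34. The four rows do not share one SE.

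**2. Table 2 with the SD of 2 on the change.** Simulating the stated model (2 pre, 3 post) gives 0.99, 0.95, 0.91 and 0.71 for the four increases. The last two rows miss by 7 to 8 points. Other placements of the group variance (five groups, or group-by-visit variation) come within 2.3 to 3 points of all rows. All of these let group variance enter the pre-post contrast, and they reject in about 35-44% of studies when the true effect is zero.

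**3. Size of the error if the SD of 2 is on the change.** The true SE of the mean change is about √(2²/6 + 4.83/50) = √(0.667 + 0.097) = 0.874. A resident-level test sees a sample variance of about 4.83 + 4 × (50 − 418/50)/49 = 8.23 (418 is the sum of squared group sizes), so its SE is √(8.23/50) = 0.406. The true SE is 0.874/0.406 = 2.15 times larger. The critical value 2.68 (49 df) acts as 2.68/2.15 = 1.24, and the false-positive rate is about 21%. Simulation gives 22-24%.

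A valid t-test on six group mean changes has critical value 4.03 (5 df) and noncentrality 2.5/0.874 = 2.86. Its power at 2.5 points is about 0.28.

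**4. Simulated false-positive rates at nominal 1%.** Where two figures are given, they are for 3 and 5 post visits. The ICC is the assumed group share of a total effect variance of 4.

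| Group variation in the change | Intercept-only model | Resident-level stage effect added | t-test on six group means |
|---|---|---|---|
| none (SD 2 on level only) | 11.6% / 16.4% | 1.1% / 1.0% | 0.9% / 1.0% |
| ICC 0.05 | 16% / 22% | 2.2% / 2.5% | 0.9% |
| ICC 0.10 | 22% / 28% | 4.3% / 4.1% | 1.0% / 1.1% |
| SD 2, added to resident SD 2 | 50% / 57% | 23% / 23% | 1.0% |

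The first row of the intercept-only column has no group variance at all. That excess comes from resident-level variation in the effect that an intercept-only model ignores. The group-specific part is best read in the next column.

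**The case against.** The strongest reply is that the plain reading is harmless. Where section 2.6 means variation in the effect, it says so: "variability in effect between subjects SD 2 (so the effect is 2.5 with SD of 2". The group SD carries no such words, so it most naturally describes level, and an idle simulation input is not an analysis error. This stands in part. A reader might infer that the SD of 2 shows the planned test to be badly liberal; the document does not support that, because it never places the SD on the change. But the level reading leaves Table 2 unexplained.

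A reader might also take the failure to reproduce Table 2 as proof that it is wrong. It is not: the simulation is only partly described.

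A third tempting reading charges the whole 16-22% rate at ICC 0.05 to the missing group term. Most of it is present at zero group variance. It belongs to a separate gap, and rests on taking the subject effect to be an intercept only, which section 3.1 does not say.

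Likewise, low power of the six-means test is partly the price of 5 degrees of freedom. At a 1-point increase with no group variation in the change it has power of about 0.37, against 0.72 for the resident-level test.

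Finally, these are enrolment waves in one home. Each lasts up to 6 + 36 + 24 = 66 weeks, so waves may overlap and share seasons or outbreaks. Six independent groups is itself an assumption, and such shocks are mainly a confounding problem. That stands as a limit on the remedy.

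An article may leave degrees of freedom and nesting to a SAP. Here, though, it names both the fixed and the random effect, and they disagree with its own simulation inputs.

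**Conclusion.** The mismatch between sections 2.6 and 3.1 is real; its consequence is conditional. With the SD of 2 on level, omitting group is harmless, but the stated inputs do not yield the 0.84 and 0.94 in Table 2. With it on the change, the stated model rejects a true null in about 50-59% of studies (the upper end includes runs without resident variation in the effect), and the 0.99 at 2.5 points is not attainable by a valid group-level test. Between these, at an assumed ICC of 0.05 to 0.10 for which the plan gives no figure, the group-specific inflation is from 1% to about 2-4% once the stage effect varies by resident.

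The figures rest on complete, balanced, normally distributed data and apply to SPPB. They do not carry over to falls, which section 2.8 names as primary.

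**What to change.** In section 2.6, state whether the between-group SD of 2 refers to SPPB level or to the effect, and recompute Table 2 by fitting the section 3.1 model to the simulated data.

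In section 3.1, let the stage effect vary by resident and by start group, with subject nested in group and Kenward-Roger or Satterthwaite degrees of freedom. A random intercept for group alone would not help. Report the t-test on the six group mean changes as a sensitivity check.

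The cost is a longer model sentence and a rerun of the 1000 simulated studies. Section 3.1 already summarises baseline data by group, so no new data are needed. The price is a wider interval and less favourable stated power. The group term corrects the standard error only; it does not remove calendar-time confounding from an uncontrolled pre-post comparison.

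### The mixed model specifies no random subject-by-stage effect, although the sample size assumes that the SPPB effect varies between residents with SD 2; on the usual random-intercept reading the SE is too small by a factor of about 1.6 to 1.9

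*Protocol article*

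**What the plan says.** Protocol article, section 3.1, gives the model: "A mixed-effects model will be computed, with treatment stage (i.e., pre- vs. post-intervention) as a fixed effect and subject as a random effect". Stage is placed in the fixed part and subject in the random part. No random stage effect, group effect or significance level is given there.

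Sections 2.1 and 3.1 schedule seven primary-outcome visits per resident: two before the intervention (weeks 0 and 6 of the baseline period), three during it (weeks 12, 24 and 36) and two afterwards (12 and 24 weeks). The text does not say which of the five later visits form the post-intervention stage.

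Section 2.6 describes the sample-size simulation: "Using the Short Physical Performance Battery (SPPB) as the primary outcome measure with 50 subjects". Its parameters are "average response at baseline 5; between-subject SD 2.5"; "variability in effect between subjects SD 2 (so the effect is 2.5 with SD of 2"); and "within-subject SD of 1; and between-group SD of 2". The level used is 1%: "the increased mean responses anticipated with alpha 0.01 are shown in Table 2".

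**The concern.** The sample size treats residents as responding differently, with a spread of individual effects twice the visit-to-visit noise. The design makes this plausible: section 2.4.2 lets the mix of interventions depend on each resident's needs, and Table 1 gives some residents an exercise programme and others virtual cycling.

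A model with only a random intercept has no term for this variation. It passes into the residual, where it is treated as independent noise at each visit and averaged down over visits. In fact a resident's own deviation in effect is shared by all of that resident's later visits, so extra visits do not reduce it. The standard error of the stage effect is then too small. The study has no randomised control, so the claim of effectiveness on SPPB would rest on this pre-post contrast and its interval.

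**Working it through.** **Inputs.** From section 2.6: n = 50, effect SD 2 (variance 4), within-subject SD 1 (variance 1). The between-subject SD of 2.5 and the between-group SD of 2, taken as differences in level, cancel from within-resident change. From sections 2.1 and 3.1: a = 2 baseline visits and m = 3 (intervention only) or m = 5 (all later visits). Assumptions: complete data, each visit entered separately, two-sided tests.

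**The plan's own figure.** Table 2 gives power 0.99 / 0.94 / 0.84 / 0.63 for mean increases of 2.5 / 2 / 1.75 / 1. Simulation from the stated parameters with 2 baseline and 3 intervention visits gives about 1.00 / 1.00 / 1.00 / 0.71 with a random stage effect and 1.00 / 1.00 / 1.00 / 0.95 with a random intercept only. Neither reproduces the table. The closest variant tried was 1 pre and 2 post values, a group SD of 2 on the effect itself, and a random-intercept test at one-sided 1%. It gave 0.98 / 0.93 / 0.86 / 0.63, with a largest gap of 2.5 points. Table 2 therefore does not show which model was fitted in the simulation.

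**True standard error.** With balanced data the stage estimate is the average over residents of (later mean minus baseline mean). Its SE is √[(4 + 1/a + 1/m)/n].
- m = 3: √[(4 + 0.500 + 0.333)/50] = √(4.833/50) = 0.311
- m = 5: √[(4 + 0.500 + 0.200)/50] = √(4.700/50) = 0.307

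**Standard error reported by a random-intercept model.** The residual pools the subject-by-stage mean square, with expectation E = 1 + 4am/(a+m) on 49 df, with pure visit noise of variance 1 on 50(a+m−2) df.
- m = 3: E = 1 + 24/5 = 5.80. Pooled residual = (49×5.80 + 150)/199 = 2.18. SE = √(2.18×0.833/50) = 0.191
- m = 5: E = 1 + 40/7 = 6.71. Pooled residual = (49×6.71 + 250)/299 = 1.94. SE = √(1.94×0.700/50) = 0.165

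**Consequence.** With r = true SE / model SE, the rejection rate at a zero mean effect is 2[1 − Φ(2.576/r)] for a nominal 1% test. The coverage of a 95% interval is 2Φ(1.96/r) − 1, whatever the mean effect.

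| Visits (pre/later) | r | Rejection at nominal 1%, formula | Simulation | 95% coverage, formula | Simulation |
|---|---|---|---|---|---|
| 2/3 | 1.63 | 11.4% | 11.5% | 77% | 76% |
| 2/5 | 1.86 | 16.7% | 16.5% | 71% | 71% |

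Fitting the random-intercept model with a mixed-model routine to a smaller set of simulated null trials gave 12.7% and 16.7%. At a nominal 5% level the simulated rates are about 24% and 29%.

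**Sensitivity (nominal 1%, random intercept only).**
- Visit layout at effect SD 2: 2/2 gives 8%, 2/1 gives 4%, 1/1 gives 1%.
- Effect SD, for 2/3 and 2/5 visits: SD 1.5 gives 8% and 12%; SD 1 gives 5% and 7%; SD 0.5 gives 2% and 2%; SD 0 gives 1% and 1%.
- n = 60 gives practically the same results as n = 50.

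**With a random stage effect by subject** (for balanced data, a one-sample t-test on each resident's mean change), the simulated rate at nominal 1% is 1.0% for both layouts.

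**The case against.** The strongest reply is that section 3.1 never says intercept only. It is one sentence in a condensed article, and the random-effects structure could be set out in a fuller plan that is not shown. The authors plainly knew that effects vary. This stands as a limit on the claim: a reader might infer that the model certainly omits a random stage effect, and the text does not go that far. It does not remove the point. The sentence assigns stage to the fixed part and subject alone to the random part, and an analysis plan that follows it on its ordinary reading inherits the problem.

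A reader might also infer an unconditional false-positive rate of 11% to 17%. The article does not support that, for three reasons.
- The range needs three or five later visits entered separately. If only the two follow-up visits count as post-intervention, the rate is about 8%.
- It needs heterogeneity of SD 2 around a zero mean, whereas section 2.6 ties that SD to an effect of 2.5. If the intervention affects no resident, the rate stays at 1%. The loss of coverage, however, does not depend on the mean effect.
- The 1% level appears only in the sample-size section.

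Nor can it be said that the power simulation used a different model: section 2.6 does not name the model fitted, and Table 2 does not reveal it.

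Finally, the figures apply to SPPB. Section 2.8 names falls as primary and lists SPPB among other measures, while Table 3 lists SPPB as primary. Nothing here gives an error rate for fall counts, QOL-ACC or Frail-NH.

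**Conclusion.** The point holds in conditional form. The stated model has no term for variation that the plan's own sample size assumes. On the usual random-intercept reading, with the scheduled visits entered separately, n = 50, effect SD 2 and within-subject SD 1, the SPPB standard error is 0.19 instead of 0.31 (2/3 visits) or 0.165 instead of 0.307 (2/5 visits). Under those conditions the intervals are materially too narrow and the test rejects too often. The problem shrinks with less heterogeneity or fewer visits and disappears with no heterogeneity or a single value before and after. Because this concerns an analysis the article states, and not merely a detail it leaves out, it should be corrected before the data are analysed.

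**What to change.** - Specify a random intercept and a random stage effect by subject (in lme4 notation, `1 + stage | subject`) with small-sample degrees of freedom.
- Name a fallback for non-convergence: subject-cluster-robust standard errors, or a one-sample t-test on each resident's mean change.
- State which of the five later visits count as post-intervention.
- Confirm that the power simulation fits the same model, or rerun it so that it does.

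The cost is a few lines of wording and a wider but correct interval. With the between-group SD acting on the level only and 2/3 visits, power at two-sided 1% stays near 1.00 for SPPB increases of 1.75 or more and is about 0.71 for an increase of 1. If the group SD of 2 also acted on the effect, the simulated figures would be about 0.95 / 0.85 / 0.78 / 0.47 for increases of 2.5 / 2 / 1.75 / 1, so the rerun should say where that SD enters.

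### The only stated model has no time term, so the stage effect is a pre–post change that includes any untreated change, of unknown sign and size, over an undefined gap of about 27 to 57 weeks

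*Protocol article*

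**What the plan says.** Section 2.1 of the protocol article describes the design: "This is a pragmatic, non-randomised, pre–post design study", in which "six groups of up to 10 participants will start the intervention at different times". The interval between starts is not given. On the run-in it says "Each group will commence a baseline period lasting six weeks".

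Section 3.1 sets the visits. "Primary outcome measures will be collected twice in the control period at week 0 and week 6". Later visits fall at weeks 12, 24 and 36 of the intervention (t1 to t3), and then "at 12 weeks and 24 weeks post-intervention for each group" (t4 and t5).

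The same section gives the analysis: "A mixed-effects model will be computed, with treatment stage (i.e., pre- vs. post-intervention) as a fixed effect", with subject as the random effect. No other quantitative model appears, and the only sensitivity analysis named is multiple imputation of missing data. Section 2.6 powers the same pre–post contrast, and its list of parameters contains no time trend. The matched sample in section 2.10 is used for hospital leave days in the economic evaluation, not for the clinical outcomes.

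**The concern.** Each resident is compared with himself or herself some months earlier. With stage as the only fixed effect, the model attributes the whole difference to the intervention. The subject effect removes stable differences between residents but not change within a resident. Staggered starts do not help while time is left out of the model, because every resident's own contrast still spans the same gap.

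Section 1 describes about 95% of residents in aged care as frail or pre-frail, so a flat untreated course over more than a year cannot be taken for granted. If residents would otherwise decline, a useful programme looks weaker than it is. If the home is improving for other reasons, or enrolment scores regress to the mean, the programme looks better than it is. Section 1.1 asks whether the service model is effective, and section 5 sends the results into provider guidelines, so the distinction affects what may be concluded.

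**Working it through.** **1. The article's own figure.** Table 2 gives power 0.99, 0.94, 0.84 and 0.63 for SPPB changes of 2.5, 2, 1.75 and 1 (n = 50, alpha 0.01). Section 2.6 gives effect SD 2 and within-subject SD 1. Take power = Φ(d/SE − 2.576), two-sided, with SE = √[(2² + 1²(1/n_pre + 1/n_post))/50].

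- One pre and one post visit: SE = √(6/50) = 0.346; power 1.00, 0.999, 0.993, 0.62.
- Two pre and five post visits: SE = √(4.7/50) = 0.307; power 1.00, 1.00, 0.999, 0.75.

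No variant tried reproduces all four rows. The power figures below are therefore relative to this calculation (0.75 at a change of 1), not to Table 2. The bias does not depend on them.

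**2. The gap.** In weeks from the start of baseline, pre visits are at 0 and 6 (mean 3). Adding the 6-week baseline, later visits are at 18, 30, 42, 54 and 66.

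| Visits counted as post | Mean week | Gap (weeks) | Bias per unit of annual drift |
|---|---|---|---|
| t1–t5 | 42 | 39 | 39/52 = 0.75 |
| t1–t3 | 30 | 27 | 27/52 = 0.52 |
| t4–t5 | 60 | 57 | 57/52 = 1.10 |

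If weeks are counted from enrolment instead, t1–t5 gives 33 weeks, inside this range. Generalised least squares with the section 2.6 SDs returns 0.75 at every stagger tried (4, 6, 8 and 12 weeks; assumed).

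**3. Size on the SPPB.** The untreated rates are assumptions.

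| Assumed change per year | 27 weeks | 39 weeks | 57 weeks |
|---|---|---|---|
| -0.25 | -0.13 | -0.19 | -0.27 |
| -0.5 | -0.26 | -0.38 | -0.55 |
| -1 | -0.52 | -0.75 | -1.10 |

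The smallest change in Table 2 is 1 point. In simulation (t1–t5 as post) with no true effect and no effect heterogeneity, the stage-only model rejects, in the direction of harm, in 15%, 71% and 100% of runs at nominal 1%. With linear time added, the rate is about 1%.

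**4. Power for a true 1-point effect at -0.5 a year.** The expected estimate is 1 − 0.375 = 0.625.

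- With a random stage effect of SD 2 added: Φ(1/0.307 − 2.576) = 0.75 falls to Φ(0.625/0.307 − 2.576) = 0.29.
- With a random intercept only, as section 3.1 states it, simulated rejection falls from 0.97 to 0.74. Those rates are inflated, because that model's SE is too small when effects vary between residents; that is a separate matter.

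**5. What a time term does** (random stage effect included, staggers of 4 to 12 weeks).

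| Model | SE | Drift left, per -1 a year | Building effect (true post mean 0.80) | Waning effect (true post mean 0.70) |
|---|---|---|---|---|
| Stage only | 0.307 | -0.75 | 0.80 | 0.70 |
| + linear weeks | 0.339 | 0 | 0.27–0.29 | about 1.5 |
| + 12-week periods | 0.35–0.40 | -0.03 to -0.06 | 0.24–0.33 | 1.2–1.3 |

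The last two columns assume no drift. The building effect rises linearly to 1 at intervention week 36 and holds: (1/3 + 2/3 + 1 + 1 + 1)/5 = 0.80. The waning effect is 1 at t1–t3, 0.5 at t4 and 0 at t5: 3.5/5 = 0.70.

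**The case against.** The strongest objection is to the obvious remedy. A reader might infer that linear time should simply go into the main model. The last table shows why that does not follow. Both adjusted models assume a constant effect, so with no drift at all they turn a building effect of 0.80 into about 0.3, and a waning effect of 0.70 into 1.2 to 1.5. These errors, about -0.5 and +0.5 to +0.8, are as large as most of the drift biases in question. Calendar periods fail in the same direction as linear weeks, so they are no check on it. Both patterns are assumed, but they are plausible for a programme with 25 weeks of exercise, then maintenance, then withdrawal (Table 1, section 2.1). This objection stands and shapes the fix.

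It can also be said that the study is openly pre–post and that section 1.1 asks about change from baseline. That makes the stage-only estimate legitimate as a description. It does not make it an effectiveness estimate, and the design holds information on time that the model discards.

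An unseen analysis plan may add covariates. But the fixed effect is stated here, so this is more than a detail left out.

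**Conclusion.** The point holds in a limited form. The stage coefficient estimates the pre–post change including untreated change. The bias is 0.75 times the annual drift if t1–t5 are all post, and about 0.5 to 1.1 times across the readings the article leaves open.

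Three stronger readings are not supported:

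- That the trial is biased against the intervention. No drift rate is given, so neither sign nor size is known; decline would hide benefit, and secular improvement or regression to the mean would inflate it.
- That power falls from 0.75 to 0.29. This needs both an assumed drift of -0.5 a year and a random stage effect with SD 2, which section 3.1 does not state.
- That 39 weeks is fixed. It depends on an undefined word.

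The figures apply to the visit-based outcomes (SPPB, Frail-NH, QOL-ACC). They do not cover fall counts, which compare periods rather than visits. The amount of calendar overlap between stages is also an assumption, since the start interval is not given.

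**What to change.** In section 3.1:

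1. Keep the stage-only estimate, labelled as the pre–post change including any untreated change.
2. Pre-specify beside it the same model with calendar time as a fixed effect, once as linear weeks and once as 12-week periods.
3. State which visits count as post, and report t1–t3 and t4–t5 separately.
4. Claim effectiveness only where the stage-only and time-adjusted results agree.

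The change is to analysis wording, provided that visit dates are captured; section 2.7 does not say so explicitly, and this should be confirmed. The SE rises by about 10% with linear weeks (0.339/0.307) and by 14% to 30% with periods (0.351/0.307 to 0.399/0.307), assuming staggers of 4 to 12 weeks. With linear weeks, power for a 1-point change goes from 0.75 to Φ(1/0.339 − 2.576) = 0.65. The adjusted models understate an effect that builds and overstate one that wanes. They should therefore accompany the stage-only estimate, not replace it, and the report should say so.
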